**Study Day 175  $\pm$ 7 Days**

1. Perform directed history and assessment of any physical complaint.
2. Record vital signs.
3. Obtain urine for dipstick testing.
4. Obtain blood for anti-Pfs25 ELISA.

**Study Day 270 ±14 Days**

1. Obtain informed consent for Version 4, if subject is willing.
2. Perform directed history and assessment of any physical complaint.
3. Record vital signs.
4. Obtain blood for CBC with differential and platelet count.
5. Obtain urine for dipstick testing.
6. For females, obtain urine for  $\beta$ -hCG testing.
7. Obtain blood for anti-Pfs25 ELISA.

**Group 2 subjects who do not receive optional booster dose****Study Day 480 ±14 Days**

1. Perform directed history and assessment of any physical complaint.
2. Record vital signs.
3. Obtain blood for anti-Pfs25 ELISA, and T and B cell studies.

**Group 2 and select high-responders in Group 1****Study Day 300 ±14 Days (Day of Third or Fourth Vaccination-approximately 6 months since third vaccination for Group 2, up to 9 months after second vaccination for Group 1)**

1. Perform basic history and focused physical examination, emphasizing examination of any acute complaints.
2. Review criteria for vaccination.
3. Obtain blood for CBC with differential and platelet count, ALT, creatinine, anti-Pfs25 antibody ELISA, and B and T cell studies.
4. For females, obtain a urine or serum sample for  $\beta$ -hCG testing. Ensure that the test is negative before vaccinating; a positive test will exclude the subject from vaccination. Review pregnancy prevention counseling.
5. Obtain a urine sample for dipstick testing and ensure that protein and blood are no more than trace positive before vaccinating. Should a female subject be menstruating on the day of vaccination, she will not be excluded from vaccination if she has more than trace blood in her urine.
6. Record vital signs (blood pressure, temperature, heart rate, and respiratory rate).
7. Administer the vaccine.
8. Observe for at least 30 minutes after vaccination to evaluate for immediate adverse reactions.
9. Review of proper use of digital thermometer, injection-site reaction measurement tool, and memory enhancement card (diary) by study staff during 30-minute post-immunization wait period. Study staff will also discuss signs and symptoms of potential AEs, and indications for use of antipyretics (acetaminophen or ibuprofen) if fever, headache, or malaise occurs.

**Study Day 303 ±1 Day (3 Days after Booster Vaccination)**

1. Perform basic history and focused physical examination (including injection site), emphasizing examination of any acute complaints.
2. Review memory enhancement card.
3. Record vital signs.

4. Obtain blood for CBC with differential and platelet count, ALT, and creatinine.

**Study Day 307  $\pm$ 1 Day (7 Days after Booster Vaccination)**

1. Perform basic history and focused physical examination (including injection site), emphasizing examination of any acute complaints.
2. Record vital signs.
3. Review memory enhancement card.
4. Obtain urine for dipstick testing.

**Study Day 314  $\pm$ 2 Days (14 Days after Booster Vaccination)**

1. Perform basic history and assessment of any physical complaint.
2. Record vital signs.
3. Obtain urine for dipstick testing.
4. For females, obtain urine or serum for  $\beta$ -hCG testing.
5. Obtain blood for CBC with differential and platelet count, ALT, creatinine, anti-Pfs25 ELISA, B and T cells, and SMFA.
6. Review pregnancy prevention counseling.

**Study Day 328  $\pm$ 3 Days (28 Days after Booster Vaccination)**

1. Perform basic history and assessment of any physical complaint.
2. Record vital signs.
3. Obtain urine for dipstick testing.
4. Review pregnancy prevention counseling.
5. Obtain blood for anti-Pfs25 ELISA

**Study Day 356  $\pm$ 7 Days (56 days after Booster Vaccination)**

1. Perform directed history and assessment of any physical complaint.
2. Record vital signs.
3. Obtain urine for dipstick testing.
4. Review pregnancy prevention counseling.
5. Obtain blood for anti-Pfs25 ELISA and SMFA.

**Study Day 450  $\pm$ 14 Days (150 days after Booster Vaccination)**

1. Perform directed history and assessment of any physical complaint.
2. Record vital signs.
3. Obtain urine for dipstick testing.
4. Obtain blood for anti-Pfs25 ELISA.

**Study Day 540  $\pm$ 14 Days**

1. Perform directed history and assessment of any physical complaint.
2. Record vital signs.
3. Obtain urine for dipstick testing.
4. Obtain blood for anti-Pfs25 ELISA.

### **Study Day 660 ±14 Days**

1. Perform directed history and assessment of any physical complaint.
2. Record vital signs.
3. Obtain blood for anti-Pfs25 ELISA, and T and B cell studies.

### **6.5 Large Volume Blood Draw**

Selected subjects with a high antibody response may be invited to undergo an optional large volume blood draw approximately 4 weeks after their third vaccination and/or last vaccination. This will be done under a separate IRB approved protocol and consent (CIR 236-Phlebotomy for collection of Serum, Plasma, and/or Leukocytes for In Vitro Studies). Up to 400 mL of blood will be drawn. Continued participation in the study will NOT be dependent on agreement to undergo this blood draw. Subjects with a hemoglobin <12.5 gm/dL on day 14 after their last vaccination will not be eligible for this blood draw. Subjects will be instructed to eat a large meal and drink several glasses of fluids (caffeine – free) prior to their phlebotomy.

Samples obtained from this blood draw will be used to create a high titer reference standard reagent. Fifty percent of serum per subject derived from this blood draw will be provided, as de-identified samples, to LMVR, a designated laboratory of the PATH Malaria Vaccine Initiative (MVI) for generation of reference standard reagents. This reference serum will be used for research purposes only and will not have any commercial use or value. PBMCs may also be obtained.

### **6.6 Symptom Memory Enhancement Card**

Subjects will be asked to keep daily symptom memory enhancement cards for recording oral temperature once during the day, as well as pain, redness, swelling at the injection site and any systemic signs or symptoms for 6 days following each immunization. The size of any injection-site reaction will be measured using a standardized clear plastic measurement tool and recorded in the memory enhancement card. Clinical site staff will review these cards and record on the source document the daily temperature, injection site erythema, swelling, induration, pain and any other sign or symptom noted by the subject. Systemic symptoms such as fever, headache, nausea, malaise, myalgia, arthralgia and urticaria (see [Table 3](#)) will be solicited from the subjects. The memory enhancement cards will not be collected.

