### **All Groups**

#### **Study Day 0 (Day of First Vaccination)**

1. Verify that Informed Consent was obtained.
2. Ensure that all inclusion/exclusion criteria are met.
3. Ensure that CBC, ALT, and creatinine measurements from screening tests are within protocol-defined limits ([Section 4.4](#) Exclusion Criteria) before vaccinating.
4. Perform interim history and physical examination, focusing on any acute complaints.
5. Obtain blood for CBC with differential and platelet count, ALT, creatinine, anti-Pfs25 antibody ELISA, SMFA, and B and T cell studies.
6. Obtain a urine sample for dipstick testing and ensure that protein and blood are no more than

trace positive before vaccinating. Should a female subject have more than trace blood in her urine on Day 0, she will not be excluded from vaccination if she is currently menstruating.

7. For females, obtain a urine or serum sample for  $\beta$ -hCG testing. Ensure that the test is negative before vaccinating; a positive test will exclude the subject from the trial. Pregnancy prevention counseling will be performed.
8. Record vital signs (blood pressure, temperature, heart rate, and respiratory rate).
9. Administer the vaccine.
10. Observe for at least 30 minutes after vaccination to evaluate for immediate adverse reactions.
11. Education by study staff during 30-minute post-immunization wait period, describing proper use of digital thermometer, injection-site reaction measurement, and malaria vaccine side-effect memory enhancement card. Study staff will also discuss signs and symptoms of potential AEs, and indications for use of antipyretics (acetaminophen or ibuprofen) if fever, headache, or malaise occurs.

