## 9.3 Assessment of Adverse Events

Assessment of safety will include clinical observation and monitoring of hematological, chemical, and immunologic parameters. Subjects will be closely monitored for 30 minutes following each immunization. Additionally, subjects will return to the clinic on Days 3, 7, 14, and 28 following each vaccination for clinical assessments, and periodically thereafter until completion. All AEs will be recorded through Day 28 after each vaccination. Injection site reactions will be assessed until day 14 or until resolved. After that period only SAEs, UPs, and NOCIs ([Section 9.1](#)) will be recorded.

All AEs will be graded for severity and assessed for relationship to the study product. Reactions

will be graded as described in this protocol. A study clinician will be available 24 hours a day during the study period. Should a subject call a study clinician to report an AE, it will be fully documented in the subject's study chart, and discussed with the PI.

All local and systemic reactions will be captured on the appropriate source documents and CRIMSON Data System. Those assessed as serious will be further reported on the Sponsor's SAE/UP report form. AEs judged to be possibly, probably, or definitely related to the study product will be followed to adequate resolution. All concomitant medications will be collected through day 28 after each vaccination; new chronic medications will be collected for the remainder of the study.

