#### **9.5 Halting Rules**

The PI will closely monitor study data as they become available and will make determinations regarding the presence and grading of AEs. The AEs will be evaluated with regard to the known complications associated with administration of vaccine components. If a dose of vaccine is considered unacceptably reactogenic (as described in the following criteria), the study will be halted. No new enrollments and no further vaccinations will be administered by the Investigators until reviewed by the SMC and study IND Sponsor. A report of SMC recommendations will be submitted to the IRBs. The following criteria will be used to define unacceptable reactogenicity of the malaria vaccine (AEs that are possibly, probably, or definitely related to the vaccine will be considered "Related" as per [Table 4](#) and will be summarized as such):

1. One or more subjects experience an SAE as defined in [Section 9.1](#) of this protocol that is determined to be possibly, probably, or definitely related to the vaccine, **or**
2. One or more subjects experience a hypersensitivity reaction that is probably or definitely related to the vaccine, **or**
3. Any severe clinical illness occurs that is not explained by a diagnosis that is unrelated to vaccination, **or**
4. Two or more subjects in any dose cohort experience any Grade 2 or higher laboratory abnormality (see [Appendix C](#)), or Grade 3 systemic AE that is determined to be possibly, probably, or definitely related to the vaccine as defined in this protocol, **or**
5. One or more subjects experience erythema nodosum.
6. Two or more volunteers in a single dose cohort experience Grade 3 or higher injection site induration or any abscess formation.

The IRBs, the NIAID, the FDA, or other government agencies may discontinue the study at any time. Subsequent review of serious, unexpected, and related AEs by the SMC or IRB, the IND sponsor, the FDA, and other regulatory authorities may also result in suspension of further administration of vaccine at the clinical site. The FDA, other regulatory authorities, and the study sponsor(s) retain the authority to suspend additional enrollment and administration of vaccine for the entire study as applicable.

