| Diarrhea                                              | 2 – 3 loose stools or < 400 gms/24 hours                 | 4 – 5 stools or 400 – 800 gms/24 hours                                                   | 6 or more watery stools or > 800gms/24 hours or requires outpatient IV hydration | ER visit or hospitalization                           |
| Headache                                              | No interference with activity                            | Repeated use of non-narcotic pain reliever > 24 hours or some interference with activity | Significant; any use of narcotic pain reliever or prevents daily activity        | ER visit or hospitalization                           |
| Fatigue/Malaise                                       | No interference with activity                            | Repeated use of non-narcotic pain reliever > 24 hours or some interference with activity | any use of narcotic pain reliever or prevents daily activity                     | ER visit or hospitalization                           |
| Myalgia                                               | No interference with activity                            | Repeated use of non-narcotic pain reliever > 24 hours or some interference with activity | any use of narcotic pain reliever or prevents daily activity                     | ER visit or hospitalization                           |
| Arthralgia                                            | No interference with activity                            | Repeated use of non-narcotic pain reliever > 24 hours or some interference with activity | any use of narcotic pain reliever or prevents daily activity                     | ER visit or hospitalization                           |
| Urticaria                                             | No interference with activity                            | Requiring PO or topical treatment > 24 hours or IV medications or steroids for ≤24 hours | Requiring IV medication or steroids for >24 hours                                | ER visit or hospitalization                           |

\* Subject should be at rest for all vital sign measurements.

\*\* Oral temperature; no recent hot or cold beverages or smoking.

\*\*\* When resting heart rate is between 60 – 100 beats per minute. Use clinical judgment when characterizing bradycardia among some healthy subject populations, for example, conditioned athletes.

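### The single daily home temperature has no stated timing relative to antipyretic intake, so fever incidence and grade can be under-recorded by an amount the protocol does not allow one to estimate

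*Protocol*

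**What the plan says.** Section 6.6 asks subjects to keep a daily card, "recording oral temperature once during the day", together with local reactions and "any systemic signs or symptoms for 6 days following each immunization". Staff then "record on the source document the daily temperature, injection site erythema, swelling, induration, pain and any other sign or symptom noted by the subject". Drug intake is not named among the items recorded or transcribed. The section adds: "The memory enhancement cards will not be collected".

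Section 6.4 (Study Day 0, item 11) has staff discuss with subjects the "indications for use of antipyretics (acetaminophen or ibuprofen) if fever, headache, or malaise occurs". The same item recurs at the second, third and booster vaccinations.

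Other provisions bear on the point:

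- Section 9.3: "All concomitant medications will be collected through day 28 after each vaccination". It also makes a study clinician available around the clock.
- Section 6.4: vital signs are recorded at the visits 3 and 7 days after each vaccination, each with a window of 1 day either side.
- Section 6.6 and Table 3: fever is one of seven solicited systemic events.
- Appendix C: fever is graded on oral temperature, 38.0–38.4 °C (Grade 1), 38.5–38.9 °C (Grade 2) and 39.0–40 °C (Grade 3). The footnote on measurement conditions covers beverages and smoking only.
- Section 3.2.1: the primary endpoint is incidence and severity of AEs.
- Section 9.5, item 4: halting can follow when two or more subjects in a dose cohort have a "Grade 3 systemic AE that is determined to be possibly, probably, or definitely related to the vaccine".

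**The concern.** Fever is graded from a measured temperature, and at home there is one measurement a day. The drugs that staff discuss act on that measurement. They may be taken for headache or malaise as well as for fever, so a subject can treat a headache, take the day's reading afterwards, and record a treated temperature. Even without a drug, one reading at an arbitrary hour can miss the day's peak. Either way the recorded value can only be at or below the peak, so any error in the fever data runs in one direction.

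This is a first-in-human trial whose primary endpoint includes AE severity, and Grade 3 fever can count towards halting. A down-graded fever would make the vaccine look milder than it was. Because the cards are not kept, anything staff do not transcribe cannot be checked afterwards.

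**Working it through.** **1. What each safeguard recovers.** Section 6.6 covers 6 days after each dose, and the Day 7 visit reviews a card for Days 0–6.

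- *Clinic vital signs.* On Day 0 they are listed before the injection. On the nominal schedule, Day 3 is the only other clinic reading within Days 0–6, and Day 7 falls just after. The evening of Day 0 and Days 1, 2, 4, 5 and 6 rest on the home reading.
- *Concomitant medications.* These show that a drug was taken. No section requires its time relative to the temperature reading.
- *Solicited fever.* A subject can report having felt feverish, but Appendix C grades fever on a temperature, so an unmeasured peak has no grade.
- *24-hour clinician.* This helps only if the subject calls.

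**2. How far a grade could move (illustration).** The protocol gives no antipyretic effect. Assume a lowering of 0.5–1.0 °C at the time of the reading:

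- 39.0 − 0.5 = 38.5 °C and 39.0 − 1.0 = 38.0 °C: a Grade 3 peak is recorded as Grade 2 or Grade 1.
- 38.4 − 0.5 = 37.9 °C: a Grade 1 peak is recorded as no fever.

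**3. The protocol's own detection figures.** Section 11.4 states a probability of at least 0.80 of seeing one or more serious or severe AEs. With P = 1 − (1 − p)^n:

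- n = 5, p = 0.275: 1 − 0.725^5 = 0.7997.
- n = 30, p = 0.052: 1 − 0.948^30 = 0.7985.

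Both agree with 0.80 to rounding. Both take it that every event is captured.

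**4. Effect of incomplete capture (illustration).** Let s be the share of subjects with a true Grade 3 fever whose recorded grade is also 3. The protocol gives no s, so it is ranged from 1.0 to 0.5. Replace p by q = sp. For Halting Rule 4 reached through Grade 3 fever alone, P(two or more) = 1 − (1 − q)^n − nq(1 − q)^(n−1). The true rates p = 0.20 and p = 0.10 are also assumptions.

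| s | One or more, n = 5, p = 0.275 | One or more, n = 30, p = 0.052 | Rule 4, n = 5, p = 0.20 | Rule 4, n = 20, p = 0.10 |
|---|---|---|---|---|
| 1.0 | 0.80 | 0.80 | 0.26 | 0.61 |
| 0.9 | 0.76 | 0.76 | 0.22 | 0.55 |
| 0.8 | 0.71 | 0.72 | 0.18 | 0.48 |
| 0.7 | 0.66 | 0.67 | 0.15 | 0.41 |
| 0.5 | 0.52 | 0.55 | 0.08 | 0.26 |

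These overstate the effect on safety detection as a whole. They treat fever as the only severe event, whereas severe events of other kinds do not depend on the thermometer.

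**The case against.** The case on the other side is substantial.

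- A reader might infer that subjects are told to take antipyretics. The protocol does not say so. Staff discuss indications should symptoms occur, which is conditional education and not prophylaxis.
- A reader might infer that drug use goes unrecorded. It does not: all concomitant medications are collected through Day 28. The card itself is not reproduced, so its exact fields are unknown. Only the timing relative to the reading is left unaddressed.
- A reader might infer that headache, malaise, myalgia, arthralgia and pain cannot be graded because the card names no drug item. Appendix C's Grade 2 for the systemic symptoms reads "Repeated use of non-narcotic pain reliever > 24 hours or some interference with activity", and pain has a similar alternative. Interference with activity is therefore enough, and the investigator assigns the grade after history and card review on Days 3 and 7.
- Someone who takes a drug because of fever has already noticed the fever and can report it. For incidence, the gap is mainly fever masked by a drug taken for headache or malaise. For grade, it remains wherever the peak was not measured.
- Halting does not rest on fever. It is one of seven solicited systemic events, and Rule 4 also counts laboratory abnormalities.
- The change may come too late. The end date is about September 2013 and the last visit is Day 660. The Day 300 booster is 660 − 300 = 360 days earlier, so about October 2012 at the latest. Version 6.0 is dated 9 January 2013.

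All of this stands. It narrows the point and lowers its weight, but does not supply an untreated peak temperature on the days without a clinic visit. On timing, most or all diary windows may already have closed, which leaves the reporting part of the fix as the part that still applies.

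**Conclusion.** The point holds as a limitation of data capture. Section 6.6 fixes one untimed reading a day, and nothing in the protocol relates it to antipyretic intake. Followed as written, the plan can miss or down-grade a fever peak that belongs to the primary endpoint and is one route into Halting Rule 4.

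The direction is downward, but the size is unknown. The calculations above rest on an assumed antipyretic effect, capture share and true fever rate, none of which the protocol provides. It would go too far to say that fever is in fact under-detected, or that a dose pattern is flattened; that needs rates of fever and antipyretic use the protocol does not give. No figure in the protocol is wrong on this point, and the detection probabilities in Section 11.4 reproduce. This is a cheap improvement, not an error that undermines the safety assessment.

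**What to change.** In Section 6.6:

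- keep the daily temperature, and add a reading whenever the subject feels feverish and before any antipyretic or analgesic dose;
- grade the highest reading of the day;
- have staff transcribe the time of each reading and of any such dose.

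Leave unchanged when the drugs may be taken.

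For diary periods already completed, report fever together with the number of diary days on which the concomitant-medication records show antipyretic use, and state that readings were not timed against intake.

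The cost is a card revision with a few transcribed times, slightly more diary burden, and a possibly higher reported fever rate. If readings are added partway through, note the change when fever is compared across vaccinations, because later doses would be measured more often than earlier ones.

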## **3.2 Study Endpoints**

### **3.2.1 Primary Endpoints**

The incidence and severity of systemic and local AEs

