**Study Day 56 +14 (Day of Second Vaccination)**

1. Perform basic history and focused physical examination, emphasizing examination of any acute complaints.
2. Review criteria for vaccination.
3. Obtain blood for CBC with differential and platelet count, ALT, creatinine, anti-Pfs25 antibody ELISA, and B and T cell studies.
4. For females, obtain a urine or serum sample for  $\beta$ -hCG testing. Ensure that the test is negative before vaccinating; a positive test will exclude the subject from the trial. Pregnancy prevention counseling will be reviewed.
5. Obtain a urine sample for dipstick testing and ensure that protein and blood are no more than trace positive before vaccinating. Should a female subject be menstruating on Day 56, she will not be excluded from vaccination if she has more than trace blood in her urine.
6. Record vital signs (blood pressure, temperature, heart rate, and respiratory rate).
7. Administer the vaccine.
8. Observe for at least 30 minutes after vaccination to evaluate for immediate adverse reactions.
9. Review of proper use of digital thermometer, injection-site reaction measurement tool, and memory enhancement card (diary) by study staff during 30-minute post-immunization wait period. Study staff will also discuss signs and symptoms of potential AEs, and indications for use of antipyretics (acetaminophen or ibuprofen) if fever, headache, or malaise occurs.

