**Table 3 Solicited Adverse Events**

| Systemic adverse events | Laboratory adverse events | Local reactogenicity |
|-------------------------|---------------------------|----------------------|
| Fever                   | Hemoglobin                | Injection pain       |
| Headache                | WBC                       | Injection erythema   |
| Nausea                  | ANC                       | Injection swelling   |
| Malaise                 | ALT                       | Injection induration |
| Myalgia                 | Platelet count            | Injection pruritus   |
| Arthralgia              | Creatinine                |                      |
| Urticaria               |                           |                      |

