## **13 Data Handling and Record Keeping**

### **13.1 Source Documentation**

Complete source documentation (laboratory test reports, hospital or medical records, progress notes, observations, subject diaries, etc.) is required for every study subject for the duration of the study. The subject's research record must record his/her participation in the clinical trial, the treatment received (with doses and frequency) or other concomitant medications or interventions administered, as well as any adverse reactions experienced during the trial. Selected data from source documentation and subject symptom diaries for subjects enrolled in the study will be entered into the CRIMSON Data System. The data entry is to be completed on an ongoing basis during the study. Data entered into CRIMSON shall be performed by authorized individuals. Corrections to the data system shall be tracked electronically (password protected) with time, date, individual making the correction, and what was changed. Source documentation should support the data collected in CRIMSON, and must be signed and dated by the person recording and/or reviewing the data.

The Investigator is responsible for the accuracy, completeness and timeliness of the data reported

to the Sponsor in the CRIMSON Data System. All data entered into CRIMSON should be reviewed by the Investigator and signed as required with written or electronic signature, as appropriate. Data reported in CRIMSON should be consistent with source documents or the discrepancies should be explained. Source documentation will be made available for review or audit by the Sponsor, MVI or their designees and any applicable Federal authorities.

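### Table 3 classes injection-site pruritus as solicited but Section 6.6 does not prompt for it; separately, Sections 6.6 and 13.1 disagree on whether the symptom card is a source document

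*Protocol*

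**What the plan says.** The primary endpoint (Section 3.2.1) is "The incidence and severity of systemic and local AEs". Table 3 in Section 9.3.1 sets out the solicited events; its local column has pain, erythema, swelling, induration and "Injection pruritus".

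Section 6.6 describes how the daily data are gathered:

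- Besides temperature, the subject records "pain, redness, swelling at the injection site and any systemic signs or symptoms for 6 days following each immunization".
- Staff review the card and "record on the source document the daily temperature, injection site erythema, swelling, induration, pain and any other sign or symptom noted by the subject".
- What is solicited is given as "Systemic symptoms such as fever, headache, nausea, malaise, myalgia, arthralgia and urticaria", with a pointer to Table 3.
- "The memory enhancement cards will not be collected".

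Section 13.1 states: "Complete source documentation (laboratory test reports, hospital or medical records, progress notes, observations, subject diaries, etc.) is required for every study subject". It also has data from symptom diaries entered into the study database. The visit lists in Section 6.4 treat card and diary as one thing, for example on the day of the second vaccination: "memory enhancement card (diary) by study staff".

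**The concern.** A solicited event is one every subject is asked about in the same way, so that silence can be read as absence. If pruritus carries that label but is not asked about in the daily record, its rate is not comparable with those for pain, redness and swelling, and a low figure could be mistaken for good tolerability. Section 12.5.2 names itching at the injection site as a possible reaction, so the event is expected. Section 11.2 lists adverse events as local, solicited or other and compares numbers of events in the two weeks after each vaccination, so the label and the count both reach the safety tables.

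The second issue is traceability. Between the Day 3 and Day 7 visits the card is the subject's only day-by-day record. If it stays with the subject, the step from card to staff record cannot be checked afterwards, and one section appears to require a document that another leaves uncollected.

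**Working it through.** The plan gives no figure to reproduce and no formula applies. The check is an item-by-item comparison of the text.

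**Local items in Table 3 against Section 6.6**

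| Table 3 local item | Subject's items | Staff list |
|---|---|---|
| Pain | named | named |
| Erythema (redness) | named | named |
| Swelling | named | named |
| Induration | not named | named |
| Pruritus | not named | not named |

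The subject's items cover 3 of 5 and the staff list 4 of 5. Only pruritus is in neither.

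**All of Table 3.** It has 7 systemic + 6 laboratory + 5 local = 18 items. The 7 systemic items are all in the Section 6.6 solicitation sentence. The 6 laboratory items are all tests named in Section 6.13, with draws scheduled in Section 6.4. Four local items are in the staff list. That makes 7 + 6 + 4 = 17 of 18 with a named route; the exception is pruritus.

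**Could other wording in Section 6.6 cover it?**

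1. The open category in the staff list depends on what the subject noted, so it does not prompt.
2. The solicitation sentence is confined to systemic symptoms.
3. The instruction to measure any injection-site reaction helps with induration, which has a diameter. It does not help with itching, which has none.

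**Doses affected.** Without boosters: 10 × 2 + 20 × 3 = 80. With a fourth dose for all of Group 2: 10 × 2 + 20 × 4 = 100. If every Group 1 subject were also boosted: 100 + 10 = 110. Sections 6.2 and 6.4 make the boosters optional or conditional, so the range is 80 to 110.

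**Card as source.** Section 6.6 has staff copy the card onto the source document and leaves the card uncollected, which points to the staff record as the source. Section 13.1 names subject diaries within the required source documentation, and Section 6.4 says the card is the diary. No sentence says that the staff record takes the card's place.

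**The case against.** The strongest case on the other side is that the card is only one route of capture. Staff take a history at Days 3, 7 and 14 after each vaccination, and examine the injection site at nearly all of those visits. Section 9.3 has site reactions followed to Day 14 or resolution and all reactions recorded. Table 3 contains laboratory results, so it was never a list of card items and may itself be the staff prompt. The card form is not shown and could carry a pruritus line.

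Much of this stands. A reader might infer that pruritus can be captured only if volunteered; the documents do not support that, because the clinic history is a second route. It does not fully close the gap. Itching is subjective, an examination cannot reliably detect it, and no visit list names it as a question. A reader might also see a grading gap because the local-reaction table in Appendix C has no pruritus row. There is none: Section 9.3.2 supplies a default scale for events not in the appendix.

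On the cards, the objection is that Section 6.6 already makes the staff record the source and that the Section 13.1 list is generic. This is a fair reading, and it means collecting the cards is only one of two ways to reconcile the sections. A reader might go further and conclude that errors in the primary endpoint cannot be found. That does not follow. The endpoint also rests on clinician assessment and laboratory reports, staff go through the card with the subject at Days 3 and 7, and Section 10.1 has monitors compare records with source. Only the copying step from card to source is uncheckable later.

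Finally, the change may come late. The protocol is Version 6.0 of 9 January 2013. With a start around September 2011, about 4 weeks of staggered first doses and a last dose at Day 300 + 14, dosing would end about 28 + 314 = 342 days after the start, before that date. The protocol's dates are approximate, so this is an inference. It is the reason the fix also covers doses already given.

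**Conclusion.** The point holds as a minor one. Section 6.6 as written does not prompt for one of the five local reactions that Table 3 calls solicited, so its rate may be under-ascertained relative to the other four. The size cannot be derived. One item in five is a count of table rows and says nothing about the share of events missed. The conclusion rests on two assumptions: that the card and source forms follow the Section 6.6 description, and that clinic history does not routinely ask about itching by name. If either form already carries a pruritus prompt, only the text needs correcting.

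The conflict between Sections 6.6 and 13.1 is real but is a matter of wording and traceability. It is not evidence of error in the primary endpoint.

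**What to change.** 1. In Section 6.6, add injection-site pruritus and induration to the items the subject records, and pruritus to the staff list. Grade pruritus on the existing Section 9.3.2 scale.
2. For doses already given without a prompt, report pruritus as unsolicited, with a footnote saying why. If no doses remain, this is the whole of the practical change.
3. Reconcile Sections 6.6 and 13.1 in one of two ways: keep and file the cards after the Day 7 review, which already takes place, or state in Section 13.1 that the staff transcription is the source and the card a memory aid. Where cards can no longer be retrieved, only the second is open.

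The cost is a line or two on the card, a sentence in Section 6.6, a table footnote, and either a clause in Section 13.1 or the filing of at most 80 to 110 cards, at one per dose.
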